## Abstract

**Background:**

Malnutrition in dependent patients has a high prevalence and can influence the prognosis associated with diverse pathologic processes, decrease quality of life, and increase morbidity-mortality and hospital admissions.

The aim of the study is to assess the effect of an educational intervention for caregivers on the nutritional status of dependent patients at risk of malnutrition.

**Methods/Design:**

Intervention study with control group, randomly allocated, of 200 patients of the Home Care Program carried out in 8 Primary Care Centers (Spain). These patients are dependent and at risk of malnutrition, older than 65, and have caregivers. The socioeconomic and educational characteristics of the patient and the caregiver are recorded. On a schedule of 0–6–12 months, patients are evaluated as follows: Mini Nutritional Assessment (MNA), food intake, dentures, degree of dependency (*Barthel test*), cognitive state (*Pfeiffer test*), mood status (*Yesavage test*), and anthropometric and serum parameters of nutritional status: albumin, prealbumin, transferrin, haemoglobin, lymphocyte count, iron, and ferritin.

Prior to the intervention, the educational procedure and the design of educational material are standardized among nurses. The nurses conduct an initial session for caregivers and then monitor the education impact at home every month (4 visits) up to 6 months. The North American Nursing Diagnosis Association (NANDA) methodology will be used. The investigators will study the effect of the intervention with caregivers on the patient’s nutritional status using the MNA test, diet, anthropometry, and biochemical parameters.

Bivariate normal test statistics and multivariate models will be created to adjust the effect of the intervention.

The SPSS/PC program will be used for statistical analysis.

**Discussion:**

The nutritional status of dependent patients has been little studied. This study allows us to know nutritional risk from different points of view: diet, anthropometry and biochemistry in dependent patients at nutritional risk and to assess the effect of a nutritional education intervention. The design with random allocation, inclusion of all patients, validated methods, caregivers’ education and standardization between nurses allows us to obtain valuable information about nutritional status and prevention.

**Trial Registration number:**

Clinical Trial Registration-URL: http://www.clinicaltrials.gov. Unique identifier: NCT01360775

## Background

There is evidence that malnutrition is common in the elderly and may influence the prognosis associated with several pathological processes, loss of independence, decrease of quality of life, and increase of morbidity-mortality and hospital admissions [1-3].

Malnutrition prevalence has been reported as 3–5% in free-living older adults and 11.6% to 60% in institutionalized individuals [4,5] but a recent study showed 21.3% in home care patients [5].

Educational programs for the elderly, including nutritional advice, have observed improvement in health status [6]. In Barcelona, a controlled trial was conducted in chronically ill 65-year-old patients and healthy controls. The intervention consisted of a self-care program as well as education on physical activity, nutrition, and social support; a statistically significant difference was observed in nutritional status [7].

Aging is related to a loss of functional capacity, and the role of caregiver becomes crucial to quality of life and for both prevention and treatment of malnutrition in dependent patients. A caregiver support program for hospitalized dependent patients observed that the support obtained positive results for the dependent patients [8]. In Finland, a nutrition education program based on constructive learning theory was developed to educate professional caregivers of patients with dementia. After one year, the study concluded that education had positive effects on the nutrition of patients [9].

However, educational interventions for caregivers of Alzheimer patients in France [10] and Parkinson patients in Europe [11] have not proven effective.

The Mini Nutritional Assessment Test (MNA), commonly used to assess nutritional status because it can be done quickly, has been validated for screening and assessment of malnutrition in older people, including the use of a reduced version [12-14]. Harris et al. noted that the MNA test has a sensitivity of 80% and a specificity of 90% [15]. Different programs have affirmed the ability of the geriatric nutritional risk index to assess the nutritional status of patients at home [16,17]. A study using the MNA found that 67.6% of subjects treated in a Home Care Program and 93.1% of the institutionalized subjects were malnourished or at risk of malnutrition; with adjusted data, this risk was 4.4 times higher among Home Care Program patients than institutionalized ones [18].

While the use of MNA as a screening tool is well established, the assessment of nutritional status and in particular of the changes produced by an intervention should have more specific estimator instruments. A recent study observes that age, sex, and body mass index (BMI) are responsible for 11.3% of the variability of the MNA test, whereas MNA items related to diet are responsible for 62.5% of this variability, indicating the importance of diet on the change in nutritional status. On one hand, this observation indicates that the most important items affecting improvement of nutritional status are the adequacy of the patient’s diet and, on the other, that more accurate methods of assessing food consumption are needed to determine the change in the diet [19].

Furthermore, the most important risk factors for malnutrition in elderly patients have been identified as number of teeth [20], depression [21], and dementia [22]. This indicates the importance of assessing these health problems in addition to the MNA test, and of this entire assessment being done by nurses in patient care programs at the household level [23].

A Home Care Program for dependent patients has been developed by Primary Health Care (PHC) services in our environment to guarantee continuity of care, access to services, and equality in care of these patients who for various reasons cannot go to a Primary Care Center (PCC).

The aim of the study is to assess the effect of a nutritional education intervention aimed at caregivers on the nutritional status of dependent patients at risk of malnutrition.

## Methods

### Design

The study design is a randomized controlled trial; intervention consists of nutritional education for caregivers of approximately 200 dependent patients at risk of malnutrition, conducted in the Home Care program in various PCC of the Tarragona-Reus area.

Research procedure is diagrammed in Figure 1.

**Figure 1 F1:**
[figure not shown]
Research procedure.

### Study population

Subjects will meet the following inclusion criteria: 1) participation in the Home Care program (ATDOM), 2) aged 65 years or older, 3) MNA score from 17 to 23.5 points, and 4) must have a caregiver. Exclusion criteria are: 1) MNA score outside the range of 17 to 23.5 points, 2) enteral feeding required, 3) severe dysphagia, 4) any serious illness that progresses to malnutrition, and 5) consumption of vitamin and/or dietary supplements.

### Recruitment

Random selection of 8 PCCs of the Catalan Institute of Health (ICS) in Reus and Tarragona counties, stratified to represent different geographical areas: a) 4 PCCs in 2 cities over 100,000 population (2 in Reus and 2 in Tarragona), b) 2 PCCs in the suburbs of these cities (1 in Tarragona, 1 in Reus), c) 1 PCC in a medium-sized urban area (about 30,000 inhabitants), and d) 1 PCC in rural areas.

Subjects will be recruited by initial identification in the electronic medical record (e-cap) indicating that they meet the criteria for participation, to be verified by performing a baseline MNA test.

### Randomization of groups

After subjects provide signed written informed consent, they will be classified randomly. From a common database, subjects will be computer-assigned to the intervention group and non-intervention (control) group in each PCC, proportionally to the total number of subjects. Subjects who choose not to participate in the study will be replaced by others of the same sex, age, and PCC to obtain the initial total sample of 97 subjects in each group.

### Intervention

Educational session aimed at caregivers: A one-hour, standardized educational session, conducted by a nurse in small groups of 15 caregivers will have the following content:

• Nutritional value of food.

• Designing a healthy diet.

• Advice on dietary adaptation to address the most common nutritional problems in this group, such as energy, protein, vitamin, mineral and water deficiency, and adaptation of textures.

• Recommendations on basic cooking techniques.

Monitoring of educational intervention: PCC nurses will monitor patients monthly at home up to 6 months and then at 12 months.

To provide individualized dietary advice as necessary, standardized ad hoc cards have been developed with all the predictable interventions.

Controls: Control subjects will not receive nutritional intervention; they will be visited once to complete an initial assessment and will receive regular Home Care follow-up at 6 months and 12 months.

### Training

Four 2-hour sessions will be held to standardize the procedure for nurses. Briefings are intended to standardize the procedure and train the nurses of the different PCC participants.

Content of the first briefing includes:

• Presentation of the study.

• Data collection procedures: MNA, Food Frequency Questionnaire (FFQ), Barthel, Yesavage and Pfeiffer questionnaires.

The second session will focus on the educational intervention:

• Reminder of the general concepts of nutrition and food in nutritional risk situations.

• Methodology for nutrition education aimed at the elderly dependent’s caregiver.

The third session will be aimed to train nurses for dietary assessment and detection of critical points. The objectives to achieve during the month will be set from these critical points.

The fourth session will have the following content:

• Standardization of education for caregivers.

• Creation of educational material.

• Procedures.

These sessions will be conducted by expert nutrition researchers with experience in educating health professionals.

### Outcomes Assessment

Subject variables in the intervention and non-intervention groups: These variables will be collected at baseline and except sociodemographic variables and current medical history again at 6 months (end of intervention), and 12 months. For the intervention group there is a questionnaire on adherence to the diet.

### Primary outcomes measures

Nutritional status variables: *Key variable:* MNA (Mini Nutritional Assessment) is a validated test with sensitivity and specificity for the diagnosis of malnutrition [12]. MNA has been selected as the main variable because it is the most used tool in PHC.

#### Other variables

##### Anthropometric measurements

Determination of standing height: Height will be measured at the highest point of the head, barefoot, with knees together, not bent, feet together, head up and eyes forward.

Calculation of length at knee-to-heel height (in the case of bedridden persons): With the person supine, flex the knee to an angle of 90. The measure will require 2 people: one will fix solid references at level of heel and knee, and the other will measure it with a tape measure. To estimate height, the formula of Chumlea will be used [24]:

$$\begin{array}{l} \text{Man}:\left(2.02\text{ × knee height }–\text{ cm heel}\right)–\left(0.04\text{ × age years}\right)+64.19\\ \text{Woman}:\left(1.83\text{ × knee height }–\text{ cm heel}\right)–\left(0.24\text{ × age years}\right)+84.88 \end{array}$$

Determination of body weight: Portable scale. Subject will be standing in light clothes and barefoot, with the patient at the center of the scale.

Determination of body weight when it cannot be measured: the following formula will be applied:

$$\begin{array}{l} \text{Man}:\left(\text{MUAC × }2.31\right)+(\text{CC × }1.5)–\;50.1\\ \text{Woman}:\left(\text{MUAC × }2.31\right)+(\text{CC × }1.43)–\;37.46 \end{array}$$

Middle-Upper Arm circumference (MUAC): we will use the midpoint of the arm. With arm relaxed and parallel to the body, we will determine the circumference at this point with tape, without tightening the tape [14].

Calf circumference (CC): we will follow similar instructions.

*Daily consumption of food* Food frequency questionnaire (FFQ): Knowledge of the dietary intake of individuals is a fundamental tool to assess the risk of disease. This test is validated for the population of Reus and gives information on food intake, energy, and micronutrients [25].

*Biochemical markers* The biochemical parameters to be analyzed are:

• Serum albumin and prealbumin (chemiluminescence).

• Serum transferrin (immunoturbidimetric).

• Hemoglobin, hematocrit, lymphocyte count (Coulter).

• Serum iron (colorimetric using ferrozine as chromatogenous agent).

A unique study profile will be created to analyze all these parameters in the Tarraco laboratory (ISO 9001:2000 certified ICS Tarragona laboratory). The extraction will be done in patient homes by PHC nurses. The same professional will take it to the PCC in regular temperature conditions, using the standard sample transport procedure between PHC and the central laboratory. The samples will be stored 8 days, the usual period of storage in the laboratory, and the results will be sent to the PHC within 8 days.

#### Secondary outcome measures

##### Sociodemographic variables

Age and sex will be recorded and social risk will be assessed through assessment of the family socio-scale designed and validated by Primary Health Care of Gijón [26].

##### Current medical history

Chronic diseases registered (e-cap), type of teeth (natural or dentures, and if prosthesis, good or bad fit).

##### Degree of dependency

Barthel Test or Basic Activities of Daily Living (ADL), used to make a physical functional assessment of patients. The collection is done by direct observation or by asking the patient if possible. The total score is calculated by adding the score of each activity. A higher score indicates greater independence: High dependence (<30), moderate dependence (30–60) and mild dependence (60–90) [27].

##### Cognitive function

Assessment of cognitive impairment by Pfeiffer’s test, a validated screening questionnaire of cognitive impairment, is fast and allows corrections depending on the subject’s level of education [28].

##### Mood

Rating mood of the population 65 years old and over by Yesavage Depression Scale identifies the presence of depression and sets levels. It consists of a series of questions with the responses scored as 0 or 1 point. A 5-item version will be used in this study. Scores are classified as 0–1, no depression; ≥ 2, possible depression [29].

### Caregiver variables in the intervention and non-intervention groups

These variables will be collected at baseline for both groups, except for the assessment of knowledge acquisition, which will be collected in the intervention group before the intervention, immediately after, and at 1–6–12 months thereafter.

#### Secondary outcome measures

##### Sociodemographic data

Age, sex, socioeconomic status, education, and the patient’s connections (family, volunteers, employee).

##### Knowledge acquisition

An 11-item questionnaire on basic concepts explained in the nutritional education intervention, designed by researchers.

### Statistical analysis

#### Sample size

The main variable is the MNA score. This value has an approximate average of 25.4 and standard deviation of 3.7 points in the Spanish population [15]. It is considered that variation of 2 points is a clinically relevant value. Considering a one-sided hypothesis and admitting an alpha error of 0.05 and a power of 95%, a sample of 72 subjects in each group is needed to observe a difference of 2 points in the MNA test after educational intervention with a precision of 80%. Taking into account possible losses during follow-up, the sample expands by 20% (15 subjects) so that the study includes 87 subjects in each group, a total of approximately 200 patients.

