#### Analysis strategy

Variables will be described as mean and standard deviation and percentages for quantitative and qualitative variables respectively. Comparison of quantitative variables will use Student-Fisher *T* test and analysis of variance for categorical variables and the chi-square statistical test. Standard tests (Kolmogorov-Smirnov and Shapiro-Wilks) will be used to verify the hypothesis of normal distribution of quantitative variables. If the preconditions for the application of statistical tests are fulfilled non-parametric tests will be used.

Longitudinal studies with a control group, which act in a phased manner on the caregiver-patient to see the effect on the patient, have different directions of analysis: caregiver assessment to measure acquisition of knowledge and implementation of dietary advice, and patient assessment to measure the effectiveness of educational intervention on nutritional status (MNA, diet, anthropometry, biochemistry) at 6 and 12 months in the intervention and control group and between groups.

To evaluate these effects, multivariate models of multiple linear regression and logistic regression will be created.

To measure the effect of educational intervention on the patient’s nutritional status (MNA, diet, anthropometry, biochemistry), the results will be adjusted according to degree of knowledge acquisition and implementation of dietary advice, as well as other variables that may interfere with the patient’s nutritional status such as socio-economic characteristics, caregiver education levels, and patients’ chronic diseases, dental status, degree of dependence (Barthel test), cognitive function (Pfeiffer Test), or mood (Yesavage Scale).

Initially the inclusion in the model of all variables that are part of the theoretical model will be forced, and in a second phase there will be an automatic selection by the stepwise method (backward and forward) to get reduced models.

The conditions of application of the models will be verified by standard techniques that are primarily based on analysis of the residuals.

The bilateral null hypothesis of normality, no difference and no significance of regression coefficients, will be discarded when their probability is less than 5%.

For data analysis the latest version of the software package SPSS/PC for Windows will be used.

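### The 95% power is stated for a one-sided test, but the analysis is two-sided at 5%; 72 evaluable per group then give about 90% at the planning SD

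*Protocol article*

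**What the plan says.** Four places in the protocol article bear on this.

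- **Sample size, the calculation.** The section reads "Considering a one-sided hypothesis and admitting an alpha error of 0.05 and a power of 95%, a sample of 72 subjects in each group" and goes on to say that this is what is needed to observe "a difference of 2 points in the MNA test after educational intervention with a precision of 80" per cent. It then adds 20% (15 patients) for losses, reaching 87 per group and a total of about 200.
- **Sample size, the planning values.** The MNA is given an "approximate average of 25.4 and standard deviation of 3.7 points in the Spanish population", and 2 points is taken as clinically relevant.
- **Analysis strategy, the decision rule.** "The bilateral null hypothesis of normality, no difference and no significance of regression coefficients, will be discarded" when the probability falls below 5%. The sentence is general and exempts no outcome, so it covers the MNA comparison.
- **Study population and Randomization of groups.** Entry requires an "MNA score from 17 to 23.5 points". The randomization section gives an initial sample of 97 per group, not 87.

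**The concern.** The sample size and the analysis use different tests. A one-sided test at 0.05 has a lower critical value than a two-sided test at 5%, so power calculated for the first overstates power for the second. The paragraph is the only power statement for the main variable. A reader of a null result would take it to come from a trial with a 5% chance of missing a 2-point difference.

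Leaving both rules in the text also leaves the verdict open for any MNA result with a one-sided p-value between 0.025 and 0.05: positive under the Sample size rule, not under the Analysis strategy rule.

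Two further features make the paragraph hard to rely on. It carries two power-like percentages (95 and 80) without saying what the second means. And its SD is taken from a population whose mean lies above the trial's entry ceiling.

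**Working it through.** **Inputs.** Difference d = 2, SD s = 3.7, alpha 0.05, power 95%, 72 evaluable per group and 87 after allowance for losses (Sample size); two-sided 5% (Analysis strategy); MNA window 17 to 23.5 (Study population); 97 per group (Randomization of groups).

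**Step 1: reproduce the stated figure.** For two equal groups, n per group = 2 × [(z_alpha + z_beta) × s / d]².

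| Test | Power | z_alpha + z_beta | n before rounding | n per group |
|---|---|---|---|---|
| One-sided 0.05 | 95% | 1.645 + 1.645 | 74.1 | 75 |
| Two-sided 0.05 | 95% | 1.960 + 1.645 | 88.9 | 89 |
| Two-sided 0.05 | 90% | 1.960 + 1.282 | 71.9 | 72 |
| One-sided 0.05 | 80% | 1.645 + 0.842 | 42.3 | 43 |
| Two-sided 0.05 | 80% | 1.960 + 0.842 | 53.7 | 54 |

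For example, the first row is 2 × (3.290 × 3.7 / 2)² = 74.1. The stated one-sided inputs therefore give 75, not 72. The number 72 matches two-sided 5% with 90% power. Read as a power, 80% gives 43 or 54, never 72.

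**Step 2: power at 72 per group.** The noncentrality is d / (s × √(2/n)) = 2 / (3.7 × √(2/72)) = 3.243. With 142 degrees of freedom, the noncentral t distribution gives:

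- one-sided 0.05: 94.3% (94.5% by normal approximation), close to the stated 95%;
- two-sided 0.05: 89.6% (90.0% by normal approximation).

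The two-sided type II error is 100 − 89.6 = 10.4%, about twice the 5% stated. By noncentral t, two-sided 95% power needs 90 per group, against 89 by the normal formula.

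**Step 3: after losses.** The Sample size section plans for 20%, and the text gives two enrolment figures.

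- From 87: 0.8 × 87 = 69.6, about 70 left, two-sided power 88.8%.
- From 97: 0.8 × 97 = 77.6, so 77 to 78 left, two-sided power about 92%.
- With no losses at all: 94.4% at 87 and 96.3% at 97.

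**Step 4: the SD.** No distribution confined to 17 to 23.5 can have an SD above half its range, (23.5 − 17) / 2 = 3.25. A uniform distribution there has SD 6.5 / √12 = 1.88. So 3.7 cannot be the baseline SD of enrolled patients. The comparison, however, is made after the intervention, when scores are no longer confined to the window, and the article gives no follow-up SD. Two-sided power at 72 per group for a range of SDs, all assumptions except 3.7:

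| SD | 2.9 | 3.3 | 3.7 | 4.0 | 4.5 |
|---|---|---|---|---|---|
| Power | 98% | 95% | 90% | 85% | 75% |

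**The case against.** The strongest reply is that nothing practical turns on this. About 90% power for the stated clinically relevant difference is ample, no enrolment target changes, and at 72 per group the one-sided power (94.3%) is close to the 95% claimed. If 97 per group are enrolled, as the randomization section says, two-sided power after 20% loss is still about 92%. All of that stands, and it limits the severity. It does not remove the contradiction, because the stated power is not delivered by the stated test at the number said to be needed.

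Three stronger readings are tempting, and the article does not support them.

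- **That the planning population lies outside the eligibility window.** Only its mean does (25.4 against 23.5), and the mean does not enter the formula. A normal distribution with mean 25.4 and SD 3.7 puts about 29% of people between 17 and 23.5.
- **That the true SD must be smaller, so that true power is higher.** The 3.25 limit applies to baseline MNA, not to MNA at 6 or 12 months. The Discussion describes patients in serious health with very high losses, so a larger follow-up SD cannot be excluded.
- **That the authors really used a two-sided test with 90% power and mislabelled it.** The match (71.9) is suggestive, but nothing in the text shows that this was the intention.

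**Conclusion.** The point holds as an inconsistent and overstated power. Under the two-sided 5% rule of the Analysis strategy, 72 evaluable per group give about 90% power and not 95%, given a difference of 2, SD 3.7, equal groups and a two-sample t test. The doubling of the type II error holds at that SD only; at an assumed SD of 3.3 the two-sided power would be back at 95%, and at 4.0 it would be 85%.

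A reader might infer that the trial is underpowered. It is not, at the planning values. The choice of SD is a separate weakness whose direction cannot be settled from the article: the value lacks support for patients at MNA 17 to 23.5, and the quantity that matters, the follow-up SD, is not reported. The shortfall of 3 per group (72 against 75) is minor by itself; it shows mainly that the paragraph does not describe one coherent calculation.

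**What to change.** 1. Make the Sample size section match the two-sided 5% analysis: 72 evaluable per group give about 90% power for a 2-point MNA difference at SD 3.7. Remove the one-sided assumption and the 95% figure.
2. Delete the 80% precision, or say what it denotes.
3. Reconcile 87 per group (Sample size) with 97 per group (Randomization of groups), and state the power expected after 20% loss from the figure kept.
4. Justify the SD for the enrolled population, and show power over SDs on both sides of 3.7, such as 2.9 to 4.5, labelled as assumptions.

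The cost is rewording and a short table. No extra patients are needed and the analysis does not change. The only drawback is that the stated power becomes less favourable, about 90% in place of 95%.

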Study results will be obtained for the main variable MNA test, a validated screening test with a sensitivity of 80% and a specificity of 90% [14], and also using other outcomes measures like anthropometric measurements (estimated according to standard recommendations), a validated food frequency questionnaire, and biochemical markers. Standard laboratory methodology will be followed for extraction, transport, treatment and storage of the samples, which will be frozen for simultaneous analysis to avoid analytical variability.

Losses to follow-up are a limitation of longitudinal studies. Moreover, in dependent patients, the loss is very high due to their serious health condition. The 20% increase over the minimum required sample and the effect at 6 months will be calculated for intermediate reporting in the case of subjects lost to follow-up.

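### The per-group target is 87 in the sample-size section and 97 in the randomisation section, and only 97 fits the stated total of about 200

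*Protocol article*

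**What the plan says.** All references are to the protocol article.

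- **Sample size**, assumptions: "Considering a one-sided hypothesis and admitting an alpha error of 0.05 and a power of 95"%, a relevant difference of 2 MNA points, and a "standard deviation of 3.7 points in the Spanish population". From these, "a sample of 72 subjects in each group is needed to observe a difference of 2 points".
- **Sample size**, allowance for losses: "the sample expands by 20% (15 subjects) so that the study includes 87 subjects in each group, a total of approximately 200 patients".
- **Randomization of groups**: people who decline are replaced by others matched on sex, age and centre, "to obtain the initial total sample of 97 subjects in each group".
- **Abstract** (Methods/Design) and **Design**: 200 patients and about 200 patients respectively, with no per-group number.
- **Discussion**: the allowance is again described as an enlargement of the minimum sample by 20%. On losses themselves the section says only that "in dependent patients, the loss is very high due to their serious health condition". No expected loss rate appears anywhere in the article.

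**The concern.** Two sections give the number to be included per group, and the numbers differ by 10 per group, or 20 patients overall. The sentence that justifies the sample size also contradicts itself, because its per-group figure does not add up to its own total.

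The number has practical uses. The replacement of refusals is tied to reaching the per-group target, and allocation within each centre is proportional to the total number of subjects. As written, staff could take recruitment to be complete at 174, 194 or 200. A later report could compare the achieved size with whichever figure suits, and a reader could not tell which was planned.

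The margin for losses also depends on which figure is meant. The protocol itself expects heavy loss in this population, and the two targets tolerate quite different amounts of it.

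**Working it through.** **Inputs.** From Sample size: 72 evaluable per group, enlargement of 20% (15 subjects), 87 per group, total about 200, one-sided alpha 0.05, difference 2, SD 3.7. From Randomization of groups: 97 per group. From Abstract and Design: 200 and about 200.

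**1. Reproduce the plan's 87.** 72 × 1.20 = 86.4, rounded up to 87; 87 − 72 = 15. The figures 72, 20%, 15 and 87 agree with each other, so 87 is not a misprint of 97.

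**2. Totals.**
- 2 × 87 = 174; 200 − 174 = 26, and 26/200 = 13%.
- 2 × 97 = 194; 200 − 194 = 6, and 6/200 = 3%.

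Only 97 per group can fairly be called about 200 in total.

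**3. Can 97 be derived from 72?**
- 97/72 = 1.35, an enlargement of 35%, not 20%.
- 72/(1 − 0.20) = 90, not 97.
- A margin for refusals does not explain it either, because refusals are replaced until 97 is reached.

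The article gives no route to 97.

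**4. What each target tolerates.** The largest loss that still leaves 72 evaluable is 1 − 72/N.
- N = 87: 15/87 = 17.2%.
- N = 97: 25/97 = 25.8%.

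**5. What remains under an assumed loss.** The article states no loss rate. The 20% and 25% used here are assumptions for illustration.

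| Randomised per group | 20% lost | 25% lost |
|---|---|---|
| 87 | 69.6 | 65.25 |
| 90 | 72.0 | 67.5 |
| 97 | 77.6 | 72.75 |

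**6. Power, one-sided as in the Sample size section.** Normal approximation: power = Φ(2 / (3.7 × √(2/n)) − 1.645).
- n = 72: Φ(3.243 − 1.645) = 94.5%.
- n = 69.6 (87 with 20% lost): Φ(3.189 − 1.645) = 93.9%.
- n = 77.6 (97 with 20% lost): Φ(3.367 − 1.645) = 95.7%.

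Going from 72 to 69.6 therefore costs about 0.6 percentage points.

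The Analysis strategy section tests two-sided at 5%. On that scale the same approximation gives 90.0% at 72, 88.8% to 89.2% at 69 to 70, and 91.8% to 92.2% at 77 to 78.

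**7. Side check on the base of 72.** The stated one-sided inputs give 2 × (3.7 × (1.645 + 1.645)/2)² = 74.08, or 75 per group. Power at 72 is 94.5%, so the gap is slight, but 72 is not exactly reproduced. It matches a two-sided 5% test with 90% power. This is a separate matter and does not affect steps 1 to 4.

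**The case against.** The strongest defence concerns the loss allowance. A reader might infer that the 20% was applied the wrong way round, because protecting 72 completers against a 20% loss takes 90 and not 87. The documents do not support calling that an error. Both Sample size and Discussion describe an enlargement of the sample by 20%, which is what was done, and done correctly. Neither section says that 20% of patients are expected to be lost, so the protocol cannot be said to miss its own loss assumption. This part of the defence stands. What survives it is narrower: the enlargement covers losses only up to 17.2%, and no loss rate is given against which to judge that.

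A second defence is that little is at stake statistically. On the protocol's one-sided basis, an assumed 20% loss from 87 leaves 2 to 3 patients per group too few and costs about 0.6 points of power. If 97 is the real target there is no shortfall at 20% at all. This also stands, and a claim that the trial is materially underpowered for this reason would go too far.

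A third defence is that the section governing allocation states 97 and that the totals elsewhere agree with it, so the intended figure can be guessed. That makes 87 the likely outlier but does not remove the contradiction: 87 is the only figure with a derivation, and 97 has none.

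**Conclusion.** The sample size is wrong as written. Targets of 87 and 97 per group stand side by side unreconciled, and 174 is not about 200. This rests on no assumption beyond doubling the stated figures. The discrepancy is 10 per group, 20 patients in all.

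The point about the allowance is conditional and minor. Without any assumption, 87 protects the 72 only up to 17.2% loss. If, and only if, 20% is taken as the expected loss rate, 90 per group would be needed and 87 leaves about 70, with one-sided power of about 93.9% against 94.5%. The power figures assume a difference of 2, an SD of 3.7 and a normal approximation. The remedy is a correction of the text, not a redesign.

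**What to change.** 1. State one per-group target in both Sample size and Randomization of groups, with a matching total in Sample size, Abstract and Design. Keeping 97 per group (194 in total) needs no patients beyond those already announced and leaves 72 evaluable for losses up to 25.8%.
2. In Sample size, replace the 20% (15 subjects) and the 87 accordingly.
3. State the expected loss rate and its basis, and derive the allowance as n/(1 − loss). The 25.8% is only what 97 can absorb; it is back-calculated and should not be presented as a planned rate. If the expected loss is higher, 97 is too few for 72 evaluable.
4. If another target is preferred, change every stated total with it. For example, 90 per group gives 180, which would create a new conflict with the 200 in the Abstract and the approximate 200 in Design and Sample size.
5. Label any quoted power as one-sided or two-sided. Check the base of 72 before writing the new derivation, since the stated inputs give 75. With 75, 97 per group still covers losses up to 22/97 = 22.7%.

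The cost is a text correction in four sections, with no increase in the announced sample if 97 is kept.
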